## Abstract

**Background:**

The role of non-kin caregivers, such as friends, neighbours, and acquaintances, in providing end-of-life care is significant but often overlooked in research and policy discussions. These caregivers provide extensive support for individuals in end-of-life care, in addition to or instead of family members. However, there is limited evidence in the literature regarding the experiences, burdens, and benefits of non-kin caregivers.

**Aims:**

The aim of this research is to examine the role and contributions of non-kin caregivers in end-of-life care. The study intends to uncover their experiences, associated challenges, benefits, and requirements for support.

**Methods:**

In order to achieve this objective, a mixed-methods approach will be employed, gathering data through structured questionnaires from approximately 150 non-kin caregivers and in-depth interviews with up to 25 participants. The questionnaires will measure the impact, burden, and benefits of caregiving. The Burden Scale for Family Caregivers, the Benefits of Being a Caregiver Scale, the Family Inventory of Needs, the Positive Mental Health Scale, a Graphic Closeness Scale, and selected items of the Eurofamcare Common Assessment Tool for socio-demographic and caregiving-related data will be used. Quantitative data will be analysed using IBM SPSS Statistics 28 for descriptive analysis and group comparison. The objective of the qualitative in-depth interviews is to obtain a comprehensive picture of the personal experiences, motivations and support needs of members of the non-kin caregivers cohort, who are as heterogeneous as possible in terms of gender, socio-economic status, and facility with the German language. The qualitative data from the interviews will be examined using MAXQDA software, adopting a grounded theory approach for analysis.

**Discussion:**

This research will develop a comprehensive framework that captures the nuanced experiences of non-kin caregivers at the end of life. The framework will identify areas where support for non-kin caregivers is lacking and where further research is needed.

**Trial registration:**

The study was prospectively registered in the German Clinical Trials Register (Deutsches Register Klinischer Studien) (Registration N° DRKS00033889; date of registration: 05 April 2024). The study is searchable under the International Clinical Trials Registry Platform Search Portal of the World Health Organization, under the German Clinical Trials Register number.

## Introduction

### Problem area: Demographic developments and non-kin caregivers

The number of community-based initiatives on caring and compassionate communities is increasing in several countries across the globe [1,2]. Such initiatives take a public health approach to the provision of palliative care, aimed at strengthening family and non-kin caregiver networks [3]. Recent research on psychosocial cancer care suggests a shift in attention from the common model of a primary caregiving family member towards a broader, system-based concept of caregiving families and social networks [4–6]. Several rationales might be offered to explain this trend: First, there is greater awareness of the importance of dealing with illness, care needs, death, and grief, socially. Second, the number of single-person households is rising steadily (1996: 12.7 million; 2011: 15.4 million), with the 2021 German microcensus placing more than 16.6 million in this category. Of these, 35.6% are aged 65 years and older [7,8]. Demographers expect the number of elderly people with assistance and support needs to grow rapidly; at the same time, researchers predict that family members will become less capable of providing support [9]. These phenomena coincide with the general wish of people to live and die in a familiar environment [10]. Furthermore, for economic reasons, the German health care system prioritises outpatient care over inpatient treatment. Informal care is central in end-of-life situations; thus, private support networks may enable patients to remain in their own home environment at the end of a terminal illness situation, until death [11–13].

Individuals who live alone and lack relatives to take on caring and/or nursing tasks often depend on support and companionship from non-kin (e.g. friends, acquaintances, neighbours). Even individuals who live with a partner or spouse may depend on an extended informal network of caring friends and others [6]. Little is known about non-kin caregivers. Nonetheless, in Germany, 1 out of 10 patients receives support from only friends, acquaintances, and/or neighbours [14]. Moreover, an Austrian study indicated that non-kin often play a central role in private support networks [15].

In German society, non-kin caregivers are invisible [15]. They lack statistical presence, and they are not significantly addressed within political discourse or informational events. This is particularly surprising, giving that the priority of outpatient over inpatient care, as mandated in the German Social Welfare Code V (Sozialgesetzbuch [SGB] V), will presumably become more important over time. Care support and counselling centres for family caregivers (e.g. “Fachstellen für pflegende Angehörige” and “Pflegestützpunkte” in Germany) [16–18] do not yet offer services specifically for non-kin caregivers.

The proposed project aims at addressing the largely unknown contributions, experiences, and support needs of non-kin caregivers.

### Conceptual definition: Non-kin caregivers

Different conceptualisations of informal caregiving and informal caregivers exist. Unfortunately, there is no consensus over these definitions in the scientific community and amongst key stakeholders in the long-term care sector, including the World Health Organization, the United Nations, the Organisation for Economic Co-operation and Development, the International Alliance of Carer Organizations, and the European Association Working for Carers. This poses a challenge for the comparability of research results, also across countries [19,20]. Tur-Sinai [20] derived the following essential characteristics from the diverging definitions of informal caregivers in the literature: “someone who provides care (1) at least weekly (2) to someone with a chronic illness, disability, or other long-lasting health, social or long-term care needs, (3) as part of an unpaid non-contractual voluntary work outside a professional or formal framework.” This definition encompasses both next-of-kin and non-kin caregivers. The proposed project will focus on the sub-group of non-kin caregivers (e.g. neighbours, friends) who support individuals who are living alone at the end of life. This sub-group includes co- and extra-resident caregivers [21]. Non-kin caregivers may support and accompany patients in various ways, and to various extents. Small groups of caregivers may also form a caregiving network or a caring community in which they network with professional health care providers (e.g. palliative home care or meal service providers, family practitioners).

### Current state of research

The German Survey on Volunteering (Freiwilligensurvey) revealed that, in 2014, 3.4% of the German population aged ≥14 years voluntarily provided informal support to neighbours or friends with care needs [22]. Several systematic reviews of family caregivers’ unmet needs [23] and overviews of assessment tools for the needs of family caregivers [24] in palliative and advanced cancer care have revealed some knowledge of the family caregiver situation. Specifically, in Germany, family caregivers shoulder a heavy share of caregiving tasks [25]; and across Europe and worldwide, they provide a significant and often invisible amount of care [9,20,26], taking over such tasks as housekeeping, nursing, and organising care. The physical, financial, and mental burdens of this caregiving may lead to pathological conditions requiring treatment [27–30]. Commonly, family caregivers express the need for emotional support, disease-specific knowledge, role responsibilities, self-care, and general practical support [23]. Research has also revealed the benefits and positive aspects of informal caregiving, including a sense of meaning and feelings of accomplishment [31]. However, the literature on non-kin caregiver activities is scarce. Overall, such caregivers have received little attention in gerontological and palliative care research [15,32]. The few available studies indicate that friends are more willing than neighbours to take over physical caregiving tasks. Specifically, caring friends tend to assist with a greater number of tasks and invest more hours per week than neighbours; but they are also older, on average, than the latter [13,33].

### Research gaps

Given social trends, the topic of non-kin caregiving is likely to increase in relevance. Research is needed on the characteristics of non-kin caregivers, their care recipients, and their caregiving situations. Previous research has focused on the burdens and needs of family caregivers, as well as the benefits of caregiving. However, little is known about the specific burdens, needs, and benefits of non-kin caregivers, the extent and type of care they provide, and the manner in which they network. Furthermore, research is needed to determine which support offers they may require or desire. For instance, friends, neighbours, and other non-kin caregivers might welcome opportunities for exchange with others in similar situations and, at times, access to professional or formal support.

## Materials and methods

### Trial registration

The study was prospectively registered in the German Clinical Trials Register (Deutsches Register Klinischer Studien) (Registration N° DRKS00033889; date of registration: 05 April 2024). The study is searchable under the International Clinical Trials Registry Platform Search Portal of the World Health Organization, under the German Clinical Trials Register number.

### Study aim

The proposed project aims at gaining knowledge on: (1) non-kin extra-resident caregivers for individuals at the end of life, (2) non-kin caregivers’ contributions to end-of-life care, and (3) non-kin caregivers’ experiences and support needs.

### Study design

The research will apply an explanatory, sequential, mixed-methods design [34]. Quantitative socio-demographic, caregiving, and survey data will be supplemented by qualitative interviews with non-kin caregivers, following an interim analysis (see Fig 1). The ability to draw from both qualitative data (applying a pragmatic, bottom-up, grounded theory approach [35,36]) and quantitative data will enable the construction of a broad conceptual framework of non-kin caregiving. The embedding of the quantitative and qualitative data in the interim analysis II will allow for further refinement of the recruitment strategy and interview guide, thereby enhancing the insights generated.

**Fig 1 pone.0306282.g001:**
[figure not shown]
Research procedure: Explanatory sequential design.

The core research questions will be: (a) Population: What are the characteristics of non-kin caregivers, their care recipients, and their caregiving situations? (b) Contributions to end-of-life care: To what extent (in terms of tasks and time) do non-kin caregivers contribute to care? How do non-kin caregivers differ from family caregivers, with respect to relationship quality and experienced closeness with the care recipient? How do non-kin caregivers ally with informal community-based support/caregiving networks and interact with formal caregiving structures? (c) Experiences and needs: What burdens and benefits arise from non-kin caregiving? Are there differences in the perceived burdens and benefits of caregiving within the diverse population of non-kin caregivers? What obstacles and conducive factors related to particular caregiving situations do non-kin caregivers experience (e.g. admission/discharge from hospital, initiation of formal care structures, death of the care recipient)?

The BSFC-s and BBCS were specifically developed for next-of-kin caregivers. However, individual survey items are formulated in such a way that they can be transferred to non-kin caregivers. In the proposed study, the quantitative analysis will provide an initial indication of the usability of these instruments for non-kin caregivers. A comparison will be drawn between the results for non-kin caregivers and those of previous studies on next-of-kin caregivers. For example, related to the GCS, Neyer et al. [43] hypothesised that relationships with non-kin caregivers would show lower levels of emotional closeness than next-of-kin relationships, as non-kin relationships might be primarily perceived in terms of reciprocity.

Socio-demographic and caregiving-related data will provide further background information on non-kin caregiver characteristics. The following socio-demographic and caregiving-related aspects are commonly reported in the literature and will be collected in our survey to enable comparison: age, gender, family/relationship status, ethnicity, religious preference, employment status, educational attainment, caregiver economic status, dwelling/household status, relationship to the care recipient, care recipient dwelling status, number of days/months/years of caregiving, and number of hours of care provided to the care recipient per week. Furthermore, the number of potential further non-kin caregivers and possible coordination between them, as well as possible coordination with professional services (e.g. nursing services) will be recorded. Also, the socio-demographic and caregiving-related questionnaire will be used to obtain data on written caregiving agreements and the receipt of remuneration. The collected socio-demographic and caregiving-related data will enable an (inter)national comparison to be drawn with other informal caregiver groups, based on findings reported in the literature.

Using items 27–34 of the Eurofamcare Common Assessment Tool [44], the following support dimensions will be recorded: (1) shopping, collecting prescriptions, and running other errands; (2) transporting or accompanying the patient to appointments; (3) cooking, cleaning, doing laundry, gardening, and performing other household chores; (4) maintaining and repairing the patient’s home; (5) washing, dressing, feeding, and assisting the patient in going to the toilet; (6) assisting with medication, medical treatment, and therapy; (7) making telephone calls, writing letters and/or e-mails, filling in forms; (8) managing finances; (9) providing financial support, accessing counselling and information about the patient’s illness and/or support services, and organising and managing care and support; and (10) providing emotional support, companionship, and reassurance. These aspects will be further investigated by questions relevant to the specific study population, investigating (for example) knowledge about patients’ end-of-life care preferences, existing proxies, and preferences and preparations concerning the time after death (e.g. burial or inheritance).

Inclusion criteria for the survey will be: Non-kin caregivers must be ≥18 years old and providing care at least weekly for at least 4 hours per week, as unpaid, non-contractual, voluntary work outside of a professional or formal framework [20]. Care-recipients must be ≥ 18 years old and suffering from a malignant or non-malignant life-limiting chronic disease.

According to the German Survey on Volunteering, 3.4% (approximately 2,435,400 persons) of the population aged ≥ 14 years provide informal care to neighbours or friends in Germany [22]. At the same time, the limited descriptive data on informal caregivers show that nearly 1 out of 10 caregivers provides extra-household non-kin care [25]. Considering the lead researchers’ previous recruitment experiences [45,46] and the planned recruitment strategy (see above), a convenience sample size of approximately 100–150 participants is expected, providing a comprehensive representation of the population of non-kin caregivers.

A quantitative socio-demographic assessment instrument to accompany the four validated quantitative surveys and one scale will be developed. A pretest will be performed with two to three non-kin caregivers to ensure the comprehensibility and appropriateness of the questions and the appropriateness of the length. The results of the pretest will be reviewed by the research team, the research advisory board and the project’s patient and public involvement (PPI) group in digital advisory board meeting. At the same meeting, the specifics of the recruitment strategy will be reviewed.

The recruitment period will commence on 1 December 2024 and conclude on 31 January 2026. The survey will be sent out by the project team to potential study participants named by recruitment partners, distributed via recruitment partners’ online distribution lists, and placed online by the project team. To mitigate the risk of a low response rate, the recruitment strategy will integrate national and regional public volunteering platforms, print media, social media, and caregiving and neighbourhood forums, and will involve committed participants from a previous study by [name] [47]. A short recruitment video will be developed, to encourage participation and introduce the project to potential caregivers. A public website will also be built, containing information on: (1) the project in different languages (i.e. written and multilingual videos), (2) possibilities for participation (e.g. online survey link), and (3) contact persons. Study participants will be asked if they are willing to participate in the qualitative in-depth interviews. Participants’ contact data and information regarding possible interview participation will be stored separately from the questionnaires.

For the analysis, quantitative data will be entered into IBM SPSS Statistics 28. Quantitative data will be analysed according to existing manuals, and in comparison with normative data from standard German population samples. Prior to the main analyses, data cleaning and interim analyses will be conducted. Accurate data entry will be ensured through a series of steps, including item range evaluation and outlier checking. Response data will be examined for plausibility and missing data. Data accuracy will be double-checked. Descriptive statistics will be calculated to test normality assumptions in the relevant outcome variables. Frequencies and group comparisons according to the hypotheses will be performed.

During participant recruitment, especially for the interviews, participants will be asked for their motivation to participate in the project and potential participants who decline participation will be asked for their reasons. Data on the participation rate and reasons for (non-)participation will be recorded and entered into IBM SPSS Statistics 28. Recruitment data will be used to enhance the recruitment strategy, if necessary.

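### The protocol says a convenience sample of 100–150 gives a comprehensive representation of the non-kin caregiver population, a property its recruitment cannot deliver at any sample size

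*Protocol article*

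**What the plan says.** The Quantitative survey section first gives population context: "3.4% (approximately 2,435,400 persons) of the population aged ≥ 14 years provide informal care to neighbours or friends in Germany". It then bases the sample size on the researchers' recruitment experience and planned strategy, and expects "a convenience sample size of approximately 100–150 participants is expected, providing a comprehensive representation of the population of non-kin caregivers".

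The recruitment paragraph of the same section sends the survey to people "named by recruitment partners, distributed via recruitment partners’ online distribution lists, and placed online by the project team". It adds volunteering platforms, print and social media, caregiving and neighbourhood forums, and the involvement of participants from an earlier study. On non-participation it says: "Data on the participation rate and reasons for (non-)participation will be recorded". The stated use of these data is to improve recruitment.

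The planned quantitative analysis consists of frequencies and group comparisons, a comparison with German normative samples, and comparisons with published next-of-kin and other informal caregiver results. The Abstract (Methods) describes the survey as "structured questionnaires from approximately 150 non-kin caregivers", without the lower figure.

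**The concern.** Representing a population requires either known selection probabilities or some mechanism, such as quotas or weighting, that ties the respondents to that population. A convenience sample has neither unless one is added, and none is described for the survey. The sentence therefore credits the design with a property that its own label rules out.

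Research question (a), under Study design, asks for the characteristics of non-kin caregivers, their care recipients and their caregiving situations. The answer will come from respondent frequencies. If the clause stands, a reader has the protocol's warrant to take those frequencies as describing non-kin caregivers in general. The comparisons with normative data and with next-of-kin studies are exposed in the same way: a difference could reflect who answered rather than what distinguishes non-kin carers. The resulting framework is meant to guide support measures, so the distinction has practical weight.

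**Working it through.** **1. What the stated sample size rests on.** The range 100–150 cannot be reproduced by calculation. The article gives no target precision, effect size or power, and presents the number as a recruitment expectation. That is not counted as a fault here. The cited population figure is coherent: 2,435,400 / 0.034 ≈ 71.6 million people aged 14 or over.

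**2. Does any described mechanism support representation?**
- Sampling frame or selection probabilities: none described. Entry is by referral, list, open link, media, forum or earlier-study involvement.
- Quotas or weighting for the survey: none described.
- Purposive selection for diversity: described under Qualitative interviews, for choosing interviewees only.
- Diversity measures under Quality assurance (self-assessment instrument, interpreters, advisory board advice on under-represented groups): these may broaden the sample, but they do not link it to the population in known proportions.
- Participation data: recorded to adjust recruitment, with no stated use in estimation.

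Nothing on this list delivers the claimed property.

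**3. Why sample size does not help (illustration; prevalence and ratios are assumed).** Let a trait have true prevalence p among eligible carers, and let carers with the trait be R times as likely to respond. The expected prevalence among respondents is q = pR / (pR + 1 − p). With p = 0.30:
- R = 1.5: 0.45 / 1.15 = 39.1%, a bias of 9 points
- R = 2: 0.60 / 1.30 = 46.2%, a bias of 16 points
- R = 3: 0.90 / 1.60 = 56%, a bias of 26 points

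The sample size n does not appear in the formula. For scale, random error alone at 50% prevalence would be 1.96 × √(0.25/100) = ±9.8 points at n = 100 and 1.96 × √(0.25/150) = ±8.0 points at n = 150.

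The chance that a nominal 95% interval contains the true 30% is Φ((p − q)/se + 1.96) − Φ((p − q)/se − 1.96), with se = √(q(1 − q)/n):

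| R | n = 100 | n = 150 |
|---|---|---|
| 1.5 | 54% | 37% |
| 2 | 10% | 2% |
| 3 | about 0% | about 0% |

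Coverage falls as n rises, because the interval narrows around the wrong value.

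**4. Participation rate.** For interviews, a denominator exists where interviewees come from survey respondents asked about follow-up contact. For closed partner lists it can exist. For a survey "online distribution lists, and placed online by the project team", or advertised in media and forums, the number of eligible people reached is unknown.

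**5. Abstract against methods.** About 150 against 100–150: the lower end is (150 − 100)/150 = 33% below the abstract's figure.

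**The case against.** The strongest reply is that the clause is loose wording. The same sentence openly says convenience sample, the planned analysis is descriptive, the main output is a conceptual framework, and comprehensive may simply mean broad. Other parts of the protocol do speak of heterogeneity and a range of perspectives. This lowers the weight of the point but does not remove it. The sentence speaks of representing a population, comes shortly after national prevalence figures, and no survey mechanism secures breadth either.

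Several stronger readings are tempting, and the document does not support them:
- A reader might infer that respondent percentages will be published as population percentages. No section says so. The clause permits that reading but does not plan it.
- A reader might test the sample against the 2,435,400 people cited. That figure covers ages 14 and over and any care need. Eligibility requires age 18 or over, at least weekly care of at least 4 hours per week, and an adult recipient with a life-limiting disease. Benchmarking age and gender against that survey would mix eligibility differences with selection.
- A reader might take online or well-connected carers to be over-represented as a fact. The channels make this plausible, but no figure shows it, and print media and partner referral are also used.
- A reader might assume that earlier-study participants will be respondents. The text says the strategy will involve them, not whether they will answer the survey or help to recruit.
- A reader might conclude that survey response reporting has been overlooked. Quality assurance already commits to CHERRIES, and the participation passage is aimed especially at the interviews.

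It is also fair that both sample-size figures are soft expectations with no power or precision target attached, so the abstract mismatch is minor.

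**Conclusion.** The point holds as a correction of one stated claim and of what the survey can support. The protocol credits a non-probability sample with representing its population, and nothing described for the survey provides that at 100, 150 or any other number. The conclusion follows from the recruitment description and needs no numerical assumption.

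The size of the bias is unknown. The 9 to 26 points above depend on an assumed 30% prevalence and assumed response ratios of 1.5 to 3, tied to no study variable. They show that selection can match or exceed random error, not that it will do so here. Neither the convenience design nor the absence of a power calculation is faulted. The change is worth making before recruitment opens, because the channel through which a respondent arrived cannot be reliably recovered afterwards.

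**What to change.** Replace the representation clause with a statement that the survey uses a non-probability sample that describes its respondents, that population proportions will not be inferred, and that comparisons with normative and published data are subject to selection bias. Do not attach a 95% half-width to that statement: it would bring back the population inference just disclaimed.

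Record recruitment channel at survey entry, for example with channel-specific links, and describe respondents by a few broad groups such as partner-referred versus open. Full results for every channel would be too thin. If about eight routes shared the sample equally (an assumption), each would hold 100/8 ≈ 13 to 150/8 ≈ 19 people. If earlier-study participants do answer the survey, repeat the main descriptive results without them. State a survey participation rate only where a denominator exists; the CHERRIES commitment can cover the open links. Give 100–150 in the abstract as well.

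The cost is a few sentences, minor survey set-up work and a more modest claim.
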